#### Secondary Outcome Analyses

Analyses of consumer activation, self-rated health, and chronic disease risk scores will be exploratory and are not intended to test hypotheses or infer causal effects. In the absence of a comparator group, these models will be used solely to identify potential signals of change and to inform outcome selection and sample size calculations for a future effectiveness trial.

To minimize analytic flexibility, covariates have been prespecified a priori and include age, gender, education, employment status, postcode (as a proxy socioeconomic indicator), baseline activation (CHAI), perceived disease threat, and trust in the therapeutic relationship. The practice site will be modeled as a random intercept to account for clustering at the practice level.

The proportion and patterns of missing data will be documented. If missingness exceeds 5%, multiple imputation using predictive mean matching will be applied to secondary outcome models [106]. Listwise deletion will be used for missing baseline covariates where required.

Consistent with feasibility study guidance, no formal adjustment for multiplicity will be undertaken. Effect estimates and 95% CIs will be reported descriptively to explore the direction and magnitude of potential change, without inferential interpretation of statistical significance. Sensitivity analyses for the exploratory multilevel models will include re-estimation under alternative intracluster correlation coefficient assumptions to assess the robustness of clustered models.

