#### Preliminary Effectiveness

The secondary outcomes are included to explore early signals of the intervention’s potential effectiveness and to inform future trial design. These outcomes include changes in consumer activation, self-rated health, and calculated disease risk scores. Consumer activation will be assessed using the 10-item Consumer Health Activation Index (CHAI), a validated measure of an individual’s knowledge, skills, and confidence in managing their health [96]. CHAI has demonstrated high internal reliability and predictive validity for health behavior change [27,96,103]. Self-rated health will be measured via a single-item rated on a 5-point Likert scale, which is widely used as a proxy for general health status [104]. Chronic condition risk scores will be calculated from data within the THRIVE platform at baseline and at 6 months postenrollment.

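### Secondary-outcome models combine multiple imputation with listwise deletion of incomplete covariates, and the fixed covariate list omits the own baseline for two of the three outcomes

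*Protocol article*

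**What the plan says.** The section Secondary Outcome Analyses of the protocol article gives two rules for missing data. The first is conditional: "If missingness exceeds 5%, multiple imputation using predictive mean matching will be applied to secondary outcome models". The second follows directly: "Listwise deletion will be used for missing baseline covariates where required".

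The same section fixes eight covariates in advance: age, gender, education, employment status, and then "postcode (as a proxy socioeconomic indicator), baseline activation (CHAI), perceived disease threat, and trust in the therapeutic relationship". The stated random effect is practice: "The practice site will be modeled as a random intercept to account for clustering at the practice level". The only sensitivity analysis named for these models varies the intracluster correlation.

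The section Preliminary Effectiveness describes the outcomes as changes: "These outcomes include changes in consumer activation, self-rated health, and calculated disease risk scores". Table 1 and that section show that CHAI and self-rated health are surveyed before and after the intervention, and that risk scores are computed from platform data at baseline and at 6 months. The analyses "will be exploratory and are not intended to test hypotheses or infer causal effects", but they are meant "to inform outcome selection and sample size calculations for a future effectiveness trial". Syntax for the models and the missing-data procedures is left to the SAP, which is to be preregistered before data extraction (Quantitative Data).

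**The concern.** Three things deserve attention, and they are separate from one another.

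- **The two missing-data rules pull against each other.** Once imputation is running, an incomplete covariate can be filled in the same step. Deleting the record instead throws away observed outcome data for no gain.
- **The covariate list fits one outcome better than the other two.** Baseline CHAI is the natural adjustment for follow-up CHAI. The list has no counterpart for self-rated health or for the risk scores, although each is measured at baseline and would usually be the best single predictor of its own follow-up value.
- **Engagement is available but not named.** Missing usage logs count as nonengagement (Primary Outcome Analyses), so every consenter has an engagement level. Nonusers stay in the cohort and are sent the follow-up survey (Engagement). If they respond less often and change less, an imputation that ignores engagement will overstate the average change.

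At stake are the estimates and variances carried into outcome selection and sample size for the next trial.

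**Working it through.** **Sample base.** The plan's figure reproduces. 1.96² × 0.5 × 0.5 / 0.10² = 96.04; × 1.95 = 187.3, stated as 187; × 1.15 = 215.05, stated as 215. The article gives no separate figure for the secondary models, so 215 is the base below.

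**Will imputation be triggered?** Planned dropout is 15%, three times the 5% trigger. The imputation rule and the deletion rule should therefore be expected to operate in the same models.

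**Records lost to covariate deletion.** Share lost = 1 − (1 − q)^8, for eight covariates each missing with probability q, independently (assumed; the article gives no rate).

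- q = 1%: 7.7%, or 17 of 215 lost, 198 left
- q = 2%: 14.9%, or 32 lost, 183 left
- q = 3%: 21.6%, or 46 lost, 169 left
- q = 5%: 33.7%, or 72 lost, 143 left

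Two facts pull this down. Gaps that cluster in the same people cost fewer records than independent gaps. Also, the platform link is sent only after the preintervention survey is completed (Intervention Content and User Experience), so gaps among users should be few. Consenters who stop before finishing that survey would be deleted, and all of them are nonusers.

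**Own baseline.** Let r be the correlation between an outcome's baseline and follow-up values, and assume that CHAI correlates 0.3 with that baseline and relates to follow-up only through it. All variances are standardised.

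- With the own baseline in the model, residual variance is 1 − r²: 0.840, 0.640, 0.360 for r = 0.4, 0.6, 0.8.
- Follow-up score modelled on CHAI only: 1 − (0.3r)² = 0.986, 0.968, 0.942. Ratios to the line above: 1.17, 1.51, 2.62.
- Change score modelled on CHAI only: 2(1 − r) − [0.3(1 − r)]² = 1.168, 0.786, 0.396. Ratios: 1.39, 1.23, 1.10.

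Under either form the residual variance passed to a future sample-size calculation is larger than it need be. By how much depends on a model form that the article does not state.

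**Engagement and follow-up.** Assume half are users, with a change of 0.3 SD in users and 0 in nonusers, so the true mean is 0.150 SD. Assume follow-up of 95% and 75%, which averages to the planned 85%. Users then make up 0.475 / 0.85 = 0.559 of responders, and the observed mean is 0.559 × 0.3 = 0.168 SD.

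A large simulation (400,000 people, r = 0.6, CHAI correlated 0.3 with baseline, engagement weakly related to CHAI, regression-based imputation) gave:

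- 95%/75% follow-up: true 0.153; imputed from CHAI 0.170; from CHAI and own baseline 0.170; with engagement added 0.153
- 95%/45% follow-up (70% overall, worse than planned): true 0.152; 0.202; 0.202; 0.150

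Adding the own baseline leaves the bias where it was; adding engagement removes it.

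**Risk scores.** At the plan's 50% assessment completion, about 0.5 × 215 = 108 people have a baseline score, and about 108 × 0.85 = 91 remain after 15% dropout. The others have no score at either time.

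**Stacked rows, only if used.** If pre and post rows were stacked with a practice intercept alone, the SE of change would be overstated by 1/√(1 − r): 1.58 at r = 0.6 and 2.24 at r = 0.8.

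**The case against.** The strongest reply is that much of this belongs to the SAP. The article defers missing-data syntax to it and names no imputation variables, so the absence of engagement from a short text is not an error. That stands: engagement is raised here as something to include when the rule is rewritten. It does not excuse the two rules and the covariate list, which are stated in the article and fixed in advance.

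A second reply is that the imputation rule refers to the models, not to outcomes alone, and that the deletion rule carries a qualifier. This also stands in part. A reader might infer that only outcomes are imputed, from the analysis covariates alone, so that imputation merely reproduces the complete-case result. The article does not say so. The qualifier, however, does not say when deletion applies, so the two sentences still need reconciling.

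A reader might further infer that standard errors for change are wrong because practice is the only random effect. The text does not support this. The outcomes are described as changes and records are matched by study code (Data Management), which links a person's two values; the 1.58- to 2.24-fold figure needs stacked rows, which are stated nowhere.

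Finally, the sizes are modest. The 0.018 SD shift in the 95%/75% scenario is about a quarter of the standard error of the mean change: √(2 × 0.4) / √183 = 0.066 SD at r = 0.6, before clustering.

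**Conclusion.** The point holds as a minor one. As written, records with an incomplete covariate are dropped from models that are otherwise imputed. The loss is 8% to 34% under assumed independent missingness of 1% to 5% per covariate, and probably near the low end. The covariate list lacks the own baseline for self-rated health and the risk scores; for activation it is present.

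Leaving engagement out of the imputation would give about 0.17 SD against a true 0.15 SD, on assumed effects and follow-up rates. It is tempting to read the covariate choices as the cause of that bias. They are not: in the simulation the result is 0.170 SD with or without the own baseline, so engagement-related attrition is a separate matter with a separate remedy.

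The exploratory status of these analyses limits the harm. Their stated use in sizing the next trial is the reason to correct them.

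**What to change.** In the SAP and its syntax, before data extraction:

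1. Replace listwise deletion of covariates with one multiple-imputation model covering all eight covariates and both time points of CHAI and self-rated health, with practice and log-based engagement level as auxiliary variables.
2. Add baseline self-rated health to the covariates for the self-rated health model, and the baseline risk score to those for each risk-score model.
3. Restrict the risk-score models explicitly to participants who completed the assessment, and name that group as the population to which the estimate applies.
4. State whether change scores, follow-up scores or stacked pre and post rows are modelled; if stacked, include a participant random intercept.

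Every variable is already collected. The cost is SAP and syntax work only.

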### Qualitative Data

Qualitative interview transcripts will be uploaded to NVivo (Lumivero) and analyzed using the Braun and Clarke 6-phase approach [107]. After immersing themselves in the data, the PhD candidate and research officer will code a sample of transcripts independently. Coding discrepancies will be resolved through discussion or the involvement of a supervisor (EH). Reporting will follow the COREQ (Consolidated Criteria for Reporting Qualitative Research) guidelines (Checklist 2) to ensure transparency [108].

### Ethical Considerations

The ePREVENT-360 study has received approval from the University of Wollongong Human Research Ethics Committee (2024‐274). Participation is entirely voluntary, and choosing not to participate will not affect consumer access to care or clinicians’ relationships with the University of Wollongong or their practice. Informed consent will be obtained via an online form that clearly outlines the study’s purpose, the voluntary nature of participation, and assurances regarding privacy and confidentiality.

The intervention is low-risk and designed to benefit participants by providing personalized health insights and support for preventive health behaviors. The intervention content has been carefully worded to minimize the risk of distress, particularly when communicating chronic condition risk. Participants are encouraged to consult their general practitioner or general practice nurse regarding any concerns, ensuring continuity of care. Support resources will be provided, especially regarding questions about family history of serious illness. The research team will monitor for unintended effects, and any issues raised by participants will be documented and reviewed. Participant compensation is aligned with the National Health and Medical Research Council’s [109] guidance on participant payments; gift cards will be provided to acknowledge participants’ contributions without inducing participation. Consumer participants will receive an Aus $50 (US $39) gift card upon completion of all study measures and Aus $30 (US $21) for partial completion. Clinician and consumer interview participants will receive an Aus $80 (US $57) gift card.

Access to all study data will be restricted to authorized researchers through password-protected, role-based permissions. Analysis scripts and deidentified datasets will be version-controlled, with a full audit trail maintained to ensure reproducibility. All data will be retained in the Microsoft Teams environment for 5 years before being destroyed in accordance with university policy.

Project governance is provided by a supervisory committee of 3 experienced and independent academic supervisors (HH, EH, and AB), who will oversee all elements of the study design, execution, analysis, and reporting. To ensure rigor and minimize bias, data integrity will be assessed through access records, date stamps, and reproducible analytic processes. The supervision team (HH, EH, and AB) will critically review all analyses. Given the feasibility nature of this study and the absence of high-risk intervention or large-scale recruitment, a formal data monitoring committee will not be convened.

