#### Clinician Data Collection

Preintervention and postintervention clinicians will be invited to participate in semistructured interviews. These interviews will explore key feasibility domains such as acceptability, sustainability, perceived impact, and optimization strategies. Approximately 8 to 10 clinicians (2 per practice) will be interviewed via videoconference, with sampling guided by saturation. Interviews will be guided by qualitative descriptive methodology. Interview guides are included in Multimedia Appendix 1 [66,68-91]. The time commitment for clinicians will range from 10 to 40 minutes, depending on their level of participation across survey and interview components.

Clinicians will also complete a postintervention survey. The survey includes 15 items rated on a 7-point Likert scale and captures data on intervention acceptability, perceived usefulness, and ease of implementation, impact on workflow, barriers, and summary of use.

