### Data Management

The THRIVE dashboard and clinician summary report are visible only to the consumer participant through their secure, personalized link. No identifiable or dashboard data are shared with clinicians or transferred to general practice systems. Only the consumer participant can choose to share their outputs or the clinician report.

Identifiable consumer participant information (first name and email address) will be collected solely to link preintervention and postintervention data. These identifiers will be collected within the secure University of Wollongong Qualtrics survey platform and stored separately from other study data. An independent research officer will assign each participant a unique study code to enable matching of deidentified data across time points. The linkage file containing names, emails, and study codes will be stored separately from all study datasets and will be accessible only to the independent research officer. Once the linkage process is complete, only deidentified datasets will be stored in the University of Wollongong Microsoft Teams environment, consistent with institutional data governance policies. For the interviews, the interviewer will have access to participants’ names and email addresses for scheduling and conducting interviews. Audio recordings and transcripts will be stored securely in the Microsoft Teams environment, consistent with institutional data governance policies. The research officer will deidentify transcripts and assign interview codes. These codes will be independent of those used for the quantitative data. Only deidentified data will be used for analysis.

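### Distress from risk results is a named risk, but the only recording route described is issues that participants raise, so the study as described yields no distress rate

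*Protocol article*

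**What the plan says.** Ethical Considerations says the content has been "carefully worded to minimize the risk of distress, particularly when communicating chronic condition risk." It then sets out three measures. Participants with concerns are pointed to their practice: "Participants are encouraged to consult their general practitioner or general practice nurse regarding any concerns, ensuring continuity of care." Support resources are offered. And "The research team will monitor for unintended effects, and any issues raised by participants will be documented and reviewed." No method, instrument, timing or responsible role is given for the monitoring.

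The systematic data collection is described elsewhere. The consumer surveys at baseline and 6 months cover acceptability, engagement, activation and self-rated health (Consumer Data Collection). The 15-item clinician survey "captures data on intervention acceptability, perceived usefulness, and ease of implementation, impact on workflow, barriers, and summary of use" (Clinician Data Collection). Table 1 lists engagement, acceptability, sustainability, activation, self-rated health and two disease risk scores. Interviews are planned with 18 to 20 consumers, with impact among the topics, and with 8 to 10 clinicians, with perceived impact among the topics.

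Progression Criteria bases the decision on engagement and acceptability, read alongside qualitative findings.

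**The concern.** THRIVE is largely automated. It shows users lifetime risk estimates for 23 conditions and a medical age. Distress at those results is the harm that the article itself identifies. Yet the recording it describes depends on a participant deciding to contact the research team, while the advice given to a worried participant is to see the general practitioner or nurse. The advice is not at issue. The point is that the described data flow does not follow it: nothing systematic is described that would carry such a consultation into the study's records.

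At stake is what the study can say about unintended effects when progression is discussed and the effectiveness trial is designed. A count of issues raised has no denominator of people who were asked. A low count could mean little distress or little reporting, and the described data could not tell these apart.

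**Working it through.** The article gives no distress rate or harm endpoint, so there is no figure to reproduce. The check has two parts.

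**1. Do the described instruments leave room for a distress question?**

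Tables 2 and 3 allocate every acceptability item to a technology-acceptance domain:
- Users: 3 + 2 + 2 + 3 + 2 + 1 + 4 + 1 = 18, the stated total.
- Nonusers: 1 + 4 + 2 + 1 + 1 + 2 + 1 = 12, the stated total.
- Clinicians: 7 + 3 + 1 + 2 + 1 + 1 = 15, the stated total.

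No domain is distress or unintended effects. Self-rated health is one general item and does not ask whether the results caused worry. Perceived disease threat is listed for the baseline survey, before access to the platform. The item wording is in an appendix that is not shown, so this establishes the described domains, not the wording of each item.

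**2. What could each route deliver?**

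*Inputs from the article:* 215 consumers and 50% completing the assessment (Sample Size), so 0.50 × 215 = 107.5, about 107 dashboard viewers. With the 15% dropout, 107.5 × 0.85 = 91.4, about 91. Intracluster correlation 0.05; 5 practices; 18 to 20 consumer interviews.

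*Assumptions, not in the article:* the true distress proportion p among viewers, the fraction of affected people who report unprompted, and random selection of interviewees.

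*Interviews.* Coverage is 18/215 = 8.4% to 20/215 = 9.3% of the planned sample. The chance that k interviewed users include no affected person is (1 − p)^k:

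| p | k = 20 | k = 10 |
|---|---|---|
| 1% | 82% | 90% |
| 2% | 67% | 82% |
| 5% | 36% | 60% |
| 10% | 12% | 35% |

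The k = 10 column is shown because interviewees are stratified by self-reported engagement, so some may never have seen a dashboard. Interviews are also opt-in and follow the 6-month survey, so random selection does not hold. The table illustrates scale only.

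*Spontaneous reports.* At p = 5%, 107 × 0.05 = 5.35 viewers would be affected. If 10%, 25%, 50% or 80% of them reported, the record would show about 0.5, 1.3, 2.7 or 4.3 cases. The article gives nothing with which to choose among these fractions, so the undercount has no computable size.

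*Asking every viewer.* With zero cases among n respondents, the two-sided 95% upper limit is 1 − 0.025^(1/n):
- n = 107: 3.4%
- n = 91: 4.0%

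These ignore clustering. If the correlation of 0.05 applied to distress (an assumption), the design effects would be 1 + (107/5 − 1) × 0.05 = 2.02 and 1 + (91/5 − 1) × 0.05 = 1.86. The effective sizes are 107/2.02 = 53.0 and 91/1.86 = 48.9, and the limits become about 6.7% and 7.3%. Either way the result is a bound with a denominator, which neither interviews nor spontaneous reports provide.

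**The case against.** The strongest reply is that this is a condensed article. The sentence in Ethical Considerations makes two commitments. "The research team will monitor for unintended effects" stands apart from the promise that "any issues raised by participants will be documented and reviewed," and the method behind the first may sit in the full protocol or ethics file. Survey items and interview guides are in an appendix that is not shown. The study is described as low-risk, has ethics approval and plans no safety claim.

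Much of this stands, and it rules out several stronger readings that a reader might infer:
- *Effects are recorded only if volunteered.* Not supported: monitoring by an unstated method is also promised.
- *Nothing can return from the practice.* Not supported: clinician interviews cover perceived impact, and a clinician survey is planned. These are possible routes, though not described as systematic reporting of distress.
- *Clinicians are not asked about such consultations.* Cannot be known without the items.
- *Interviews are the only solicited contact.* Wrong: a 6-month survey goes to consumers, nonusers included, and clinicians are surveyed.
- *Follow-up of a reported problem is barred because identifiers* "will be collected solely to link preintervention and postintervention data." Data Management itself lets the interviewer use names and emails, and the platform link is sent by email, so the article does not apply that wording literally.
- *Restricted dashboard visibility cuts clinicians off.* "The THRIVE dashboard and clinician summary report are visible only to the consumer participant through their secure, personalized link" concerns access to outputs, which the consumer may share. It does not decide whether a clinician can tell the study about a worried patient.

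What does not stand is that the matter is merely detail left to an appendix. The article describes a recording route, and that route is passive. It also accounts for every acceptability item by domain and lists its outcomes, and none is a harm measure.

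**Conclusion.** The point holds as a gap between a promise of monitoring and the passive recording described. Distress is named, no described outcome or survey domain elicits it, and concerns are directed to the practice without a described systematic path back. Undercounting is likely because spontaneous reporting depends on the participant's initiative. That is an inference about direction; no size can be given. The firmer consequence is that the study as described will produce no distress proportion with a denominator for the progression discussion or the future trial.

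This is an inexpensive improvement to ascertainment. It is not evidence that THRIVE causes harm, nor that the authors intend to read silence as safety. It rests on the article's description of its surveys. If the appendix or full protocol already contains a solicited distress question, what remains is to list it among the outcomes and report it.

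**What to change.** Add two or three fixed items to the existing 6-month consumer survey for everyone who viewed the dashboard: whether the risk results caused worry or distress, whether that led them to stop using THRIVE, and whether they sought care because of it. Add one item to the clinician survey on consultations prompted by worry about THRIVE results.

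Report the proportion with its 95% CI beside the acceptability results, and consider it under Progression Criteria. Usage logs record dashboard views, so the eligible denominator is known. State how many viewers answered, because anyone who left on account of distress may not return the survey.

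The cost is about a minute per respondent and an ethics amendment, for which the Protocol Modification Plan provides the route. Recall at 6 months is imperfect, and a solicited rate may look less favorable than a count of volunteered issues. Timing favors acting now: consumer recruitment began in December 2025, so the first 6-month surveys fall due around June 2026, and 25 of the planned 215 consents had been obtained by 17 April 2026. Any participants surveyed before the amendment should be reported as not asked.
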